### Ultrasound-guided subparaneural block at the brachial plexus upper trunk bifurcation

All block procedures are independently performed in full by [name], a senior anesthesiologist with extensive experience in ultrasound-guided brachial plexus block, who has completed more than 200 standardized ultrasound-guided upper trunk block procedures prior to the trial. [name] is prohibited from participating in any baseline or postoperative outcome assessments, and only obtains the pre-prepared study drug corresponding to the subject’s enrollment number from [name], the dedicated anesthesiology nurse responsible for randomization management and study drug preparation, only after [name] has fully completed all baseline pulmonary function and diaphragmatic excursion measurements and archived the original data. [name] is only aware of the injection volume of the study drug for the individual enrolled subject, and is strictly prohibited from disclosing any allocation-related information to other study personnel, the subject, or the surgical team.

The subject is placed in a standardized supine position, with the head gently rotated to the contralateral side of the surgery, and the operative upper limb kept in a neutral position without abduction throughout the procedure, to ensure stable visualization of the brachial plexus anatomical structure. The SONOSITE SII® ultrasound system (FUJIFILM SonoSite, Inc., Bothell, USA) equipped with a high-frequency (6 to 13 MHz) linear array ultrasound probe is used for pre-scanning of the target region, following a systematic anatomical localization strategy. Scanning is commenced from the neck region to accurately locate the transverse processes of the C5 to C7 cervical vertebrae and the corresponding nerve root exit sites via cross-sectional scanning; thereafter, the probe is moved distally along the course of the brachial plexus to the supraclavicular fossa region. During the scanning process, the convergence of the C5 and C6 anterior rami to form the upper trunk of the brachial plexus is clearly visualized, followed by the trifurcation of the upper trunk into the anterior division, posterior division, and suprascapular nerve at the bifurcation point in the supraclavicular fossa. The probe is slowly tilted, slid and rotated to adjust the ultrasound beam incident angle, to obtain the optimal ultrasound view where the anterior division, posterior division, and suprascapular nerve of the upper trunk are arranged in a triangular or linear pattern within the same intact paraneural sheath.

After obtaining the optimal ultrasound view, the puncture site is disinfected and sterile drapes are applied following routine clinical sterile requirements for regional anesthesia. Local infiltration anesthesia is performed at the puncture site with 1 mL of 1% lidocaine solution. A 22 G × 50 mm nerve block needle is connected to a syringe pre-filled with the study drug (0.375% ropivacaine, 2 mL for the intervention group and 5 mL for the control group, prepared by [name] in advance according to the randomization allocation). The in-plane technique is used for needle advancement, with the needle inserted from the lateral to medial direction at an angle of 30° to 45° relative to the skin (27, 28). The entire length of the needle shaft is continuously visualized under real-time ultrasound guidance throughout the advancement process.

The needle tip is advanced under continuous ultrasound monitoring to ensure accurate placement within the paraneural sheath at the bifurcation point of the upper trunk, without penetrating the nerve fascicles or violating the integrity of the paraneural sheath. After confirming the correct needle tip position, the study drug is injected into the paraneural sheath, with intermittent aspiration performed every 0.5 mL during injection to rule out intravascular or intraneural injection. The spread of the local anesthetic within the paraneural sheath is continuously monitored via real-time ultrasound throughout the injection process, to ensure circumferential spread of the drug around the three target nerve branches of the upper trunk, with no excessive diffusion toward the anterior scalene muscle or phrenic nerve region. If the subject reports paresthesia or abnormal muscle contraction during the puncture and injection process, the needle tip is immediately withdrawn, and the puncture direction is adjusted to avoid nerve injury. No additional local anesthetic is administered to any subject during the entire procedure, beyond the pre-specified volume of the study drug according to the randomization group.

Upon completion of the injection, the puncture site is covered with an opaque sterile dressing. [name] leaves the operating room immediately after the procedure, and does not participate in the subsequent general anesthesia management, intraoperative care, or postoperative outcome assessment of the subject. Any adverse events during the block procedure, including inadvertent vascular puncture, local anesthetic toxicity, persistent paresthesia, or bleeding at the puncture site, are fully documented in the subject’s case report form and electronic medical record in real time.

### Anesthesia management

#### General anesthesia induction

After the completion of the ultrasound-guided subparaneural injection at the brachial plexus upper trunk bifurcation (the study intervention). The induction regimen consists of intravenous propofol (2–3 mg/kg) and sufentanil (5 μg); the sufentanil is administered as adjuvant analgesia to complement the preoperative nerve block, ensuring adequate analgesia during induction and initial surgical stimulation.

In strict accordance with the study protocol, no muscle relaxant is administered to any subject during the entire anesthesia induction and maintenance period, to avoid any interference with the postoperative assessment of upper limb sensorimotor block and diaphragmatic motor function. No additional sedative or analgesic drugs are administered during the induction phase, except for the study intervention and the aforementioned induction agents, to eliminate confounding factors that may affect the primary and secondary outcome assessments.

After the induction of general anesthesia, a laryngeal mask airway (LMA) is inserted to manage the patient’s airway. Correct positioning of the LMA is confirmed by bilateral equal breath sounds on auscultation, stable end-tidal carbon dioxide (EtCO_2_) waveform, and no air leakage during mechanical ventilation. Mechanical ventilation is conducted in pressure-controlled mode with standardized settings: maximum airway pressure limited to 15 cm H₂O, respiratory rate set at approximately 11 breaths per minute, and inspiratory-to-expiratory ratio of 1:2. Ventilation parameters are adjusted only to maintain EtCO₂ between 35 and 45 mmHg, ensuring respiratory stability while minimizing the risk of barotrauma.

All anesthetic agents administered during the induction phase, including the specific dose, administration time, and any adverse events during induction (such as hypotension, bradycardia, allergic reaction, or airway complications), are accurately recorded in the electronic anesthesia record sheet by the attending anesthesiologist. The anesthesiologist performing the induction is strictly prohibited from inquiring about the group allocation of the subject, and all communication related to the study intervention is restricted to [name] and [name], the dedicated anesthesiology nurse responsible for study drug preparation.

#### General anesthesia maintenance

General anesthesia maintenance is performed by the same attending anesthesiologist responsible for induction, who remains fully blinded to the subject’s group allocation throughout the procedure. Consistent with the induction protocol, no neuromuscular blocking agents are administered at any point during the maintenance phase to avoid confounding interference with the core trial outcomes of postoperative diaphragmatic motor function and upper limb sensorimotor block assessments.

The primary analgesia for the procedure is provided by the preoperative study intervention (ultrasound-guided subparaneural block at the brachial plexus upper trunk bifurcation), and the following standardized stepwise protocol is strictly enforced for all intraoperative hemodynamic fluctuations related to surgical stimulation: When the subject’s intraoperative heart rate or mean arterial pressure (MAP) exceeds 20% of the preoperative baseline value, the end-tidal concentration of inhaled sevoflurane is first increased to 3%; if the heart rate and blood pressure do not return to the baseline range within 5 min, an intravenous bolus of 2.5 μg sufentanil is administered, with repeated doses of 2.5 μg sufentanil permitted if the hemodynamic response remains uncontrolled after each dose. The total dose of sufentanil administered intraoperatively is accurately recorded for each subject as a key secondary outcome of the trial.

Sedation and hypnosis are maintained with inhaled sevoflurane (end-tidal concentration 1.5–3% in 50% oxygen/air mixture). No additional intravenous sedatives are administered unless clinically required for refractory hemodynamic instability, with all such deviations fully documented as protocol violations. Mechanical ventilation is consistent with the settings described in General anesthesia induction, without modifications, and continues until the end of the surgery.

Other intraoperative hemodynamic abnormalities are managed per standardized institutional guidelines: hypotension (MAP ≥20% below preoperative baseline) is initially managed with a 250 mL lactated Ringer’s bolus, followed by 8 μg norepinephrine boluses if persistent; clinically significant bradycardia (heart rate ≤45 bpm with hemodynamic instability) is treated with intravenous atropine 0.25–0.5 mg. Fluid management follows a goal-directed protocol, with maintenance lactated Ringer’s infusion at 4–6 mL/kg/h and additional boluses titrated to intraoperative blood loss and hemodynamics. Core body temperature is maintained at 36.0–37.5 °C using a forced-air warming system throughout the procedure.

Standard continuous monitoring is maintained throughout the maintenance phase, including three-lead ECG, non-invasive blood pressure measured at 5-min intervals, continuous SpO₂, EtCO₂, end-tidal sevoflurane concentration, and nasopharyngeal temperature. All intraoperative data, including total doses of anesthetic, analgesic and vasoactive agents, anesthesia and surgery duration, fluid balance, adverse events, and protocol deviations, are fully documented in the electronic anesthesia record system, and subsequently extracted by blinded independent investigators for statistical analysis.

#### General anesthesia recovery

At the completion of the surgical procedure, the inhaled sevoflurane is discontinued immediately, and the fresh gas flow is increased to 6 L/min to accelerate the washout of the anesthetic agent from the patient’s body. Mechanical ventilation is maintained with settings consistent with those described in the general anesthesia induction section, without modifications, until spontaneous breathing is fully restored.

Extubation of the LMA is performed only when all the following extubation criteria are met: the patient regains full consciousness and can follow verbal commands; spontaneous breathing is stable, with a tidal volume ≥ 6 mL/kg predicted body weight and respiratory rate of 10–20 breaths per minute; EtCO₂ is maintained between 35 and 45 mmHg; the gag and cough reflexes are fully recovered; heart rate and mean arterial pressure remain within 20% of the preoperative baseline; and SpO₂ ≥ 95% is maintained on room air. After LMA removal, the patient is given supplemental oxygen via a face mask at 4 L/min, and transferred to the PACU accompanied by the attending anesthesiologist responsible for anesthesia management.

Upon arrival in the PACU, standard continuous monitoring is initiated immediately, including three-lead ECG, NIBP measured at 5-min intervals, continuous SpO₂, and respiratory rate monitoring. The patient’s level of consciousness, respiratory status, surgical site condition, and adverse events are assessed and documented every 15 min by PACU nursing staff who remain fully blinded to the subject’s group allocation throughout the recovery period.

Pain assessment is performed immediately after the patient regains full consciousness and can accurately report discomfort. Pain intensity is scored based on the patient’s self-reported arm or shoulder discomfort using the 11-point Numerical Rating Scale (NRS), where 0 represents no pain and 10 indicates the greatest anguish imaginable. All recorded NRS scores are the pre-rescue analgesia values. If the patient’s NRS score is greater than 3, an intravenous bolus of 5 μg sufentanil is administered, and this administration is repeated as required to achieve adequate pain control. The exact time, dose, and number of fentanyl boluses administered in the PACU are fully documented in the electronic anesthesia record system.

Discharge from the PACU is only permitted when the patient meets all the following criteria: the Aldrete recovery score is ≥ 9 points; core body temperature is maintained at 36.0–37.5 °C; hemodynamic and respiratory status are stable for at least 30 min without supplemental oxygen support; pain is well controlled with a NRS pain score ≤ 3; no severe adverse events such as persistent nausea and vomiting, dyspnea, or neurological abnormalities are observed; the required postoperative pulmonary function and diaphragmatic excursion assessments have been fully completed; and the PCA pump has been correctly initiated. All recovery-related data, including emergence time, LMA extubation time, PACU stay duration, vital signs during recovery, adverse events, and rescue analgesia administration, are fully documented in the electronic anesthesia record system and study-specific case report form (CRF) in real time.

#### Postoperative pulmonary function test and diaphragmatic excursion measurement

All postoperative pulmonary function and diaphragmatic excursion measurements are independently completed by [name], the same investigator who performed the preoperative baseline assessments, to eliminate inter-operator variability and ensure the consistency and comparability of paired pre- and post-intervention data.

The measurements are performed when the subject is fully awake, has stable spontaneous breathing, and can accurately follow standardized verbal instructions, strictly before discharge from the PACU. The subject’s body position, equipment used, operational procedures, quality control standards, and data calculation methods for the measurements are completely consistent with those used for the preoperative baseline assessments.

Hemidiaphragmatic paralysis (HDP) is defined as a decrease in postoperative diaphragmatic excursion of ≥75% compared with the baseline value, or the presence of paradoxical diaphragmatic movement during breathing. The incidence of HDP is recorded as one of the co-primary endpoints of the trial. The absolute and percentage changes in diaphragmatic excursion, forced expiratory volume in 1 s (FEV1), and forced vital capacity (FVC) from baseline to postoperative measurement are calculated for each subject as key secondary endpoints of the trial.

All postoperative measurement data are entered into a standardized CRF marked only with the subject’s unique study ID in real time, and independently double-entered into the study-specific locked electronic database by two other researchers not involved in the measurement or intervention procedures, with cross-verification performed to ensure the integrity, accuracy and traceability of the paired data.

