For diaphragmatic excursion measurement, the anterior subcostal approach is adopted by [name], with the liver (for subjects undergoing right-sided shoulder surgery) or the spleen (for subjects undergoing left-sided shoulder surgery) used as the acoustic window. The measurement is performed using the SONOSITE SII® ultrasound system (FUJIFILM SonoSite, Inc., Bothell, USA) equipped with a low-frequency (1 to 5 MHz) convex array probe. After clearly visualizing the continuous diaphragmatic pleural line, the probe position and angle are fixed, and the system is switched to M-mode to record the waveform of diaphragmatic movement during deep breathing. Three stable and reproducible diaphragmatic movement waveforms during deep breathing are continuously recorded for each subject, the excursion amplitude (cm) of the ipsilateral hemidiaphragm is measured for each valid waveform, and the average value of the three measurements is calculated and documented as the baseline diaphragmatic excursion value of the subject. All original ultrasound images of the measurements are archived in real time for subsequent review and data verification.

For pulmonary function testing, [name] uses a CONTEC SP80B handheld spirometer (CONTEC Medical Systems Co., Ltd., Hebei, China) with the subject remaining in the same standardized semi-sitting position. The subject wears a nose clip and holds a disposable mouthpiece, and completes forced expiration maneuvers following standardized verbal instructions, in strict accordance with international pulmonary function testing guidelines. Three valid and reproducible forced expiration measurements are completed for each subject, with invalid curves (such as those caused by insufficient expiratory time, poor initial expiratory burst, or air leakage) excluded. The forced expiratory volume in 1 s (FEV1) and forced vital capacity (FVC) of each valid measurement are recorded, and the average value of the three valid measurements is calculated and documented as the baseline FEV1 and FVC values of the subject. The baseline FEV1/FVC ratio is calculated simultaneously, and subjects with a baseline FEV1/FVC < 70% are excluded from the trial in accordance with the pre-specified exclusion criteria.

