### Outcomes

#### Primary outcomes

This trial adopts a dual co-primary endpoint design to simultaneously verify the non-inferiority of analgesic efficacy and the superiority of diaphragmatic safety of the 2 mL local anesthetic regimen:

1 Pre-rescue analgesia NRS pain score assessed immediately after the patient regains full consciousness in the PACU

*Evaluation tool*: 11-point NRS (0 = no pain, 10 = the worst imaginable pain)*Evaluation time*: Immediately after full consciousness and ability to accurately report discomfort, strictly before any rescue analgesia administration*Study objective*: To test the non-inferiority of 2 mL 0.375% ropivacaine compared with 5 mL 0.375% ropivacaine in postoperative analgesic efficacy, with a predefined non-inferiority margin of 1 point on the NRS scale.

2 Incidence of ipsilateral hemidiaphragmatic paralysis (HDP) assessed before discharge from the PACU

*Definition*: Complete paresis: A reduction in diaphragmatic movement of more than 75%, no movement, or paradoxical movement. Partial paresis: A reduction in diaphragmatic movement between 25 and 75%.*Evaluation tool*: Ultrasound measurement of diaphragmatic excursion via the anterior subcostal approach (M-mode)*Evaluation time*: Strictly before discharge from the PACU, performed by the same blinded investigator who conducted the baseline measurements*Study objective*: To test the superiority of 2 mL 0.375% ropivacaine compared with 5 mL 0.375% ropivacaine in reducing the risk of HDP.

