#### Sample size calculation

The sample size calculation is based on the dual co-primary endpoints of this trial: the non-inferiority of analgesic efficacy (PACU pre-rescue NRS pain score) and the superiority of diaphragmatic safety (incidence of hemidiaphragmatic paralysis, HDP). All calculations are performed using PASS 15.0.5 software (NCSS, LLC, Kaysville, UT, USA) with a one-sided significance level (*α*) of 0.025 and a statistical power (1-*β*) of 0.80, consistent with the design of randomized non-inferiority trials in anesthesiology.

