##### Sample size calculation based on HDP incidence superiority endpoint

The primary superiority endpoint is the difference in the incidence of ipsilateral HDP between the two groups. Based on the study by Zhang et al. (27), the incidence of HDP in patients receiving 5 mL 0.375% ropivacaine via subparaneural injection at the upper trunk bifurcation is 16.67%. Our preliminary study (n = 11) showed that no HDP occurred in patients receiving 2 mL 0.375% ropivacaine via the same technique, leading to our core hypothesis that the HDP incidence of the 2 mL regimen is infinitely close to 0.

However, the PASS 15.0.5 software does not allow setting the group proportion to 0 in the two-sample Z-test for superiority of proportions. To accurately reflect our preliminary findings and satisfy the software’s calculation requirements, we set the HDP incidence in the 2 mL group to an extremely small value of 1 × 10^−20^, which is mathematically indistinguishable from 0 for all practical clinical purposes.

Using the two-sample Z-test for superiority of proportions with pooled variance, the required sample size per group is calculated as follows:
$$n=\frac{{\left(Z_{1-\alpha }+Z_{1-\beta }\right)}^{2}(p_{1}(1-p_{1})+p_{2}(1-p_{2}))}{{\left(p_{1}-p_{2}\right)}^{2}}$$
Where 
$p_{1}=0.166667$
 (HDP incidence in the 5 mL group), 
$p_{2}=1\times 10^{-20}$
 (estimated HDP incidence in the 2 mL group), 
$Z_{1-\alpha }=1.96$
, and 
$Z_{1-\beta }=0.84$
. Substituting the values yields a required sample size of 40 patients per group.

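### The paradoxical-movement and no-movement limbs of the HDP co-primary ignore baseline, and no eligibility rule removes a hemidiaphragm already in that state before the block

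*Protocol article*

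**What the plan says.** The section on postoperative measurement defines HDP as "a decrease in postoperative diaphragmatic excursion of ≥75% compared with the baseline value, or the presence of paradoxical diaphragmatic movement during breathing". The Primary outcomes section defines complete paresis as "A reduction in diaphragmatic movement of more than 75%, no movement, or paradoxical movement". In the postoperative section the percentage-fall limb is tied to the patient's own pre-block value. The paradoxical limb in both sections (in the postoperative section, "or the presence of paradoxical diaphragmatic movement during breathing"), and the no-movement limb in Primary outcomes, carry no condition on how the hemidiaphragm moved before the block.

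The eligibility list under Subjects and setting is specific, with cut-offs for INR, platelets and FEV1/FVC. No item concerns the diaphragm or the phrenic nerve. The nearest items are existing nerve injury in the operative limb, earlier surgery to the shoulder or neck on the same side, and airflow obstruction.

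The baseline session takes both excursion and spirometry. For excursion, "Three stable and reproducible diaphragmatic movement waveforms during deep breathing are continuously recorded for each subject". Only spirometry leads to an exclusion there: "subjects with a baseline FEV1/FVC < 70% are excluded from the trial in accordance with the pre-specified exclusion criteria".

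**The concern.** The baseline section says the pre-block measurements exist to give paired data for the primary and secondary endpoints. Two limbs of the endpoint are unpaired. A hemidiaphragm that was paradoxical beforehand and is unchanged afterwards meets the definition, so an existing condition is recorded as a block effect.

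This matters because the co-primary rests on very few events: essentially none planned on 2 mL and about seven or eight on 5 mL. The Introduction also hopes to help define a volume at which HDP does not occur. A single misattributed case on 2 mL removes a zero-event result whatever the test shows.

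**Working it through.** **1. Following the text for each baseline state, with a block that changes nothing**

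| Ipsilateral hemidiaphragm before the block | Postoperative measurement section | Primary outcomes section |
|---|---|---|
| Paradoxical | HDP (paradoxical limb) | HDP (paradoxical limb) |
| Immobile | Neither limb met; percentage fall undefined (division by zero) | HDP (no-movement limb) |
| Reduced, normal direction | Not HDP: no fall from own baseline | Not HDP: no reduction |
| Normal | Not HDP | Not HDP |

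The fault is confined to the top two rows, and the second arises only under the Primary outcomes wording.

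**2. The plan's own sample size**

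Inputs, from the sample size sections: one-sided α 0.025 and power 0.80, giving z values of 1.96 and 0.84; p1 = 0.166667 on 5 mL; p2 = 10⁻²⁰ on 2 mL, where "we set the HDP incidence in the 2 mL group to an extremely small value".

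n = (1.96 + 0.84)² × [p1(1 − p1) + p2(1 − p2)] / (p1 − p2)² = 7.84 × 0.13889 / 0.027778 = 39.2, so 40 per arm. With 20% dropout, 40 / 0.8 = 50. Both match the plan. Expected 5 mL events are 40/6 = 6.7 and 50/6 = 8.3.

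**3. Effect of one added 2 mL event on the planned criterion**

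The criterion is that the lower one-sided 97.5% bound of the risk difference (5 mL minus 2 mL) exceeds 0. The unpooled bound is RD − 1.96 × √[p̂1(1 − p̂1)/n + p̂2(1 − p̂2)/n].

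Example, 50 per arm, 4 v 0: 0.08 − 1.96 × √(0.08 × 0.92/50) = 0.08 − 0.0752 = +0.005. At 4 v 1: 0.06 − 1.96 × √(0.001472 + 0.000392) = 0.06 − 0.0846 = −0.025.

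| 5 mL events | 50 per arm: v 0 | 50 per arm: v 1 | 40 per arm: v 0 | 40 per arm: v 1 |
|---|---|---|---|---|
| 4 | +0.005 | −0.025 | +0.007 | −0.030 |
| 5 | +0.017 | −0.012 | +0.023 | −0.013 |
| 6 | +0.030 | +0.002 | – | +0.004 |
| 7 | +0.044 | +0.016 | +0.057 | +0.023 |
| 8 | +0.058 | +0.031 | – | +0.042 |

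(7 v 0 at 40 per arm: 0.175 − 1.96 × √(0.175 × 0.825/40) = 0.175 − 0.1178 = +0.057. Dashes: not tabulated.)

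The result is reversed at 4 v 0 and 5 v 0. It stands at the expected counts, 7 v 1 at 40 per arm and 8 v 1 at 50. With a pooled Z at 50 per arm, 6 v 1 also just fails (z = 1.960 to three decimals).

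**4. How likely a reversal is, given one such case on 2 mL**

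Take 5 mL events as Binomial(n, 1/6) and no true events on 2 mL.

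- 40 per arm: power P(X ≥ 4) = 0.919 falls to P(X ≥ 6) = 0.676, a loss of 24 percentage points.
- 50 per arm, unpooled: 0.976 falls to 0.861, a loss of 11 points. With a pooled Z it falls to 0.749, a loss of 23 points.

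A case landing on 5 mL works the other way, turning a failing 3 v 0 into a passing 4 v 0. The chance is 6% at 40 per arm and 2% at 50.

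**5. Effect if a share q of both arms is affected (assumption; no figure in the documents)**

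| q | Power, 40 per arm | Power, 50 per arm (unpooled) | n per arm by the printed formula |
|---|---|---|---|
| 0 | 0.919 | 0.976 | 40 |
| 0.5% | 0.881 | 0.950 | 42 |
| 1% | 0.845 | 0.923 | 45 |
| 2% | 0.777 | 0.865 | 50 |

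The last column uses p2 = q and p1 = q + (1 − q)/6. At q = 1%: 7.84 × (0.175 × 0.825 + 0.01 × 0.99)/0.165² = 44.4, so 45.

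**The case against.** The strongest reply is that this is a rare event with a small effect. Allocation is random and the assessor is blinded, so misclassification falls on both arms alike in expectation. At an assumed 1%, power at 50 per arm stays at 0.923. Excluding earlier shoulder or neck surgery on the same side already removes one cause of phrenic injury. All of this stands, and it limits the size of the point. It does not make the scoring correct.

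Nor does condensation into an article explain the gap. The eligibility list is detailed, and the endpoint wording is a stated rule that gives the wrong answer when followed exactly.

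A reader might infer more than the documents support:

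- *That any existing diaphragm weakness is counted as HDP.* It is not. Reduced, normally directed movement is judged against its own baseline.
- *That one patient decides the superiority test at the planned event counts.* It does not at 7 v 1 or 8 v 1.
- *That 2 mL is systematically favoured or penalised.* Random allocation and blinding argue against this.
- *That patients with no usable ultrasound window are randomised and then imputed.* The block operator receives the drug only after all baseline measurements are complete, which should largely stop them. Imputation is described only for withdrawal or loss to follow-up. The same step may also stop some immobile hemidiaphragms that yield no measurable waveform, so the paradoxical case is the clearer one.
- *That small baseline excursions make the percentage change unreliable.* The documents give no measurement-error figure to support this, and three waveforms are averaged by one trained assessor.

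**Conclusion.** The point holds in a narrow form. An ipsilateral hemidiaphragm that is already paradoxical, or immobile under the Primary outcomes wording, is scored HDP even when the block has changed nothing, and no eligibility rule removes it. The cost is mainly power and precision. The reversal chances of about 11% (50 per arm, unpooled) and 24% (40 per arm) are conditional on one such patient falling in the 2 mL arm, a true 5 mL rate of 1/6 and no true 2 mL events. The chance of having such a patient cannot be derived from the documents.

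The descriptive harm does not depend on the test: one such patient turns 0/50 into 1/50, or 2%, in a trial that hopes to show none. The point is worth correcting before recruitment proceeds, because the information needed is already collected before allocation.

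**What to change.** 1. In the postoperative measurement section and in Primary outcomes, define the paradoxical and no-movement limbs as new since the baseline scan, with the same wording in both places.
2. In Subjects and setting and in the baseline measurement section, require before the envelope is opened that the baseline ipsilateral scan shows a visualised hemidiaphragm with movement that is neither absent nor paradoxical, and three reproducible waveforms. The spirometry exclusion already acts at this session.

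Both parts are useful. The definition alone would leave in the trial patients who can never register a new event under these limbs. The criterion alone would still mis-score anyone enrolled in error. No contralateral criterion is needed, since the endpoint and the scan are ipsilateral. No minimum excursion is proposed, since the documents give no basis for one.

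The cost is wording, plus possibly a few screen failures on the day of surgery. The scan, the assessor and the sample size of 40 per arm (50 with dropout) stay as they are.
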